### Eligibility, Recruitment, and Randomization

Female caregivers caring for a child born between December 1, 2019, and June 1, 2022 (aged between 15 and 45 months at the time of baseline assessment), were eligible for participation in this study. Eligible women were the primary persons responsible for childcare and not necessarily biological mothers.

Recruitment of caregivers was conducted between July 29, 2023, and September 3, 2023. Members of the project team visited prospective households, accompanied by respected women from the local communities. Eligible caregivers were enrolled in the study if they (1) provided consent to participate in the study; (2) declared their availability to attend the 3 rounds of assessments; and (3) agreed that we could, if necessary, delay their participation in the project by 1 year.

In total, 542 eligible caregivers enrolled in this study. For each village, the location of each household was determined by GPS, and mutual distances between households were computed. To prevent cross contamination, we divided groups of households into clusters. To avoid large clusters of households, we selected a subset of households that could be split into smaller clusters of no more than 5 households. The distance between households from distinct clusters was set as >100 m. Some eligible households were excluded from the study to fulfill this condition. These caregivers were invited to join savings groups a year later (refer to the Intervention section). The number of excluded households (n=99) was kept to a minimum by using advanced graph theory methods. Therefore, 443 (81.7%) female caregivers were included in this study.

Clusters, each including 1 to 5 households, were randomly assigned to the DBS, PA, or WLC group. The randomization process mimicked a block design; it considered dwelling place (village) and child age (children aged between 15 and 30 months vs children aged >30 to 45 months) and ensured a balanced distribution of these characteristics across the study groups.

The study participants were not informed which program (DBS or PA) constituted the studied intervention and which served as a control condition.

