### Data Analysis

#### Statistical Analysis Plan

All data will be analyzed by an independent statistician using R (R Foundation for Statistical Computing) or Stata (StataCorp LLC). Fidelity will first be described with standard descriptive statistics. Hypothesis tests will be 2-sided with α of .05, and effect-size statistics will be reported to indicate the magnitude of any intervention effects.

Outcomes are classified a priori as primary, secondary, or exploratory. For the primary outcomes, we will use the Holm-Bonferroni method to adjust *P* values. Secondary and exploratory outcomes will be interpreted as hypothesis generating; the Benjamini-Hochberg procedure will be applied for their significance evaluation.

The primary and secondary outcome analyses will follow the intention-to-treat principle.

Linear mixed models or, where appropriate, analyses of covariance will evaluate intervention effects at both the intensive and extensive postintervention phases, always adjusting for baseline outcome scores. Because participants are clustered, a random effect will be included, and fixed-effect estimates will be compared with intercluster variability. Before modeling, every numerical predictor will be mean centered and standardized (*z* scores); interaction terms will be created as products of these centered variables. Candidate covariates and moderators (child age, dwelling place, child sex, socioeconomic situation, and parental cognitive abilities as indexed by education) will be retained only if they are significant or if removing them markedly alters other parameter estimates.

Although the intention-to-treat approach is the primary approach, a complementary per-protocol analysis will be performed to clarify whether any lack of impact arises from deficiencies in the intervention itself or from participants’ incomplete exposure to it.

Multicollinearity among predictors will be assessed using variance inflation factors, with appropriate mitigation strategies applied where necessary.

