#### Statistical Power

The required sample size was calculated according to accepted mathematical principles (48,49].

The sample size in each of the 3 arms of the study was computed using the following formula:

where α of .05 is the significance level, ...1–β (.80) is the power of the test, and *z*_1–α/4_ (2.24) and z_1–β_ (0.84) are quantiles of the standard normal distribution. The significance level α of .05 is divided by 4—the number of comparisons performed while primary hypotheses are tested (in fact, this is the so-called Bonferroni correction). All tests have 1-sided alternatives. On the basis of the previous meta-analytic studies [52,53], power is guaranteed for the effect size of 0.5. Finally, *DE* is the so-called design effect. It takes into account the clustered nature of data and is computed using the following formula:

DE = 1 + ([cv2 + 1]m –1)ICC

where the *m* value of 3 is the expected average cluster size, *ICC* is the intracluster correlation coefficient, and *cv* is the coefficient of variation of the cluster size. We set the *IC*C at 0.05—more than twice the commonly reported value of approximately 0.02 in comparable parenting studies. This higher value inflates the design effect and, in turn, the required sample size, providing a buffer that preserves statistical power. The value of *cv*^2^=2/9 was used, corresponding to a discrete uniform distribution of cluster sizes from 1 to 5. This range reflects both the settlement layout and our clustering procedure, which aimed to retain as many eligible households as possible while keeping clusters compact (refer to the Eligibility, Recruitment, and Randomization section). Substituting these values into the formula mentioned earlier, one obtains a *DE* of 1.13.

Taking into account a potential attrition rate of up to 15%, the required sample size of each arm is 100. Observations with missing values of the outcome variable will be excluded from the analysis that deals with the given outcome but could still be included in other analyses. Missing values in covariates will be substituted by their regression estimates based on other covariates. The impact of the substitution will be discussed by comparing the current estimates with those obtained if the observations with missing values were excluded.

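### Village and child age, on which the randomisation was balanced, stay in the intervention-effect model only if significant or influential, so the confirmatory model is not fixed in advance

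*Protocol article*

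**What the plan says.** The protocol's section Eligibility, Recruitment, and Randomization describes allocating clusters of 1 to 5 households to three arms by a procedure resembling blocking: "it considered dwelling place (village) and child age" (15–30 versus >30–45 months), with balance across arms on both.

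The section Statistical Analysis Plan specifies linear mixed models or analyses of covariance for intervention effects at both post-intervention time points. Two elements are fixed: adjustment for the baseline outcome score and a random effect for clustering. Child age, dwelling place, child sex, socioeconomic situation and parental cognitive abilities are candidates, which "will be retained only if they are significant or if removing them markedly alters other parameter estimates". The rule stands in the paragraph that defines the intervention-effect models. It is not limited to moderator or sensitivity analyses, and nothing in the protocol exempts village or child age from it.

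**The concern.** Factors used to restrict a randomisation belong in the analysis because of the design, whatever their P values. Here they can leave the model on the evidence of the data.

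The second retention criterion suits them badly. Because they are balanced across arms, removing one hardly moves the treatment estimate and mainly changes its standard error. A criterion based on movement of estimates will therefore seldom keep them, and their place rests on significance alone.

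That criterion also has no threshold and covers the intervention effect itself. Two competent analysts could reach different primary models from the same data, and the choice could be made with the treatment estimate in view. The selected set may also vary across primary outcomes and between the two post-intervention assessments, so the Holm-adjusted P values could come from differently specified models.

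**Working it through.** **The plan's own figure.** The nearest stated number is 100 per arm. The formula is missing from the extracted text, so the standard two-means form is assumed: n = 2 × ((2.24 + 0.84)/0.5)² = 75.9. The design effect is 1 + ((2/9 + 1) × 3 − 1) × 0.05 = 1.133, which gives 86.0. Dividing by 0.85 gives 101.2; multiplying by 1.15 gives 98.9. The figure reproduces. No covariate adjustment enters it, so it is unaffected here.

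The checks below use two-sided 5% tests, following "Hypothesis tests will be 2-sided with α of .05". The Statistical Power section's "All tests have 1-sided alternatives" conflicts with this, but that is a separate matter.

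**Would the rule keep a balancing factor?** A two-arm contrast has about 443 × 2/3 ≈ 295 dyads. For a factor explaining a share R² of residual variance, the noncentrality is λ = 295 × R²/(1 − R²). The test is an F test at .05, with 1 df for age and 11 df for the 12 villages, ignoring clustering. The last column is the standard-error increase if the factor is dropped, 1/√(1 − R²) − 1.

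| R² | λ | Age kept | Village kept | SE increase if dropped |
|---|---|---|---|---|
| 0.02 | 6.0 | 69% | 30% | 1.0% |
| 0.05 | 15.5 | 97.5% | 74% | 2.6% |
| 0.10 | 32.8 | about 100% | 98.6% | 5.4% |
| 0.20 | 73.8 | about 100% | about 100% | 11.8% |
| 0.30 | 126.4 | about 100% | about 100% | 19.5% |

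A factor strong enough to matter is nearly always kept. The factors likely to be dropped cost little.

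**Rejection rates.** These come from simulation under assumptions that are not in the documents: two arms of 120; 12 villages × 2 age bands balanced 1:1; baseline correlation 0.5; socioeconomic and cognitive variables at 2% of variance each; no residual cluster effect. There were 3,000 null runs and 1,000 runs at a true effect of 0.3 SD. Mechanical use of the rule assumed a 10% change threshold.

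| Village/age variance share | 2%/2% | 5%/10% | 10%/20% |
|---|---|---|---|
| Type I, both always in | 5.3% | 4.8% | 5.1% |
| Type I, both always out | 4.8% | 2.4% | 1.3% |
| Type I, rule used mechanically | 5.0% | 4.8% | 4.9% |
| Type I, smallest P among permitted models | 5.6% | 5.2% | 5.2% |
| Power, both always in | 77.9% | 84.3% | 94.1% |
| Power, both always out | 76.6% | 78.9% | 83.5% |
| Power, rule used mechanically | 79.6% | 85.6% | 95.0% |

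Monte Carlo error on type I is about 0.4 points. Under the null at 2%/2%, the rule dropped village in 55% of runs and age in 23%. At 10%/20% it dropped neither. The rule's power is not below that of the model with village and age alone, because the rule can also keep the other covariates.

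**Deliberate picking.** Five candidates give 2⁵ = 32 models. With 126 per arm, no true effect and covariate slopes of 0.1, 0.2 and 0.3 SD, the most favourable model was taken while covariates significant in the full model were forced to stay, as the rule requires. Type I error was 6.0%, 5.1% and 4.8% (2,000 runs). A repeat with 3,000 runs gave 6.7%, 5.3% and 4.8%. The range is therefore about 5–7%.

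**The case against.** A reader might infer that the analysis ignores how the trial was randomised. It does not. Clusters were the randomised units and a random effect for clustering is always included, as is baseline score. Only the balancing factors and the other candidates are exposed.

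A reader might also infer serious type I inflation. If the analyst could choose freely among all 32 models, the error in the last check would be 7.9%, 9.7% and 15.7%. That requires dropping significant covariates, which the rule forbids. Likewise, a standard error 5–20% too large needs factors explaining 10–30% of residual variance to be dropped. The rule would rarely do that, so those figures are an upper bound.

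A third tempting reading is that a retained treatment-by-moderator term would change the meaning of the main effect. The protocol gives moderation its own section, Mediator and Moderator Analyses, and numerical predictors are centred, so the arm coefficient would sit near the average effect. Centring does not settle this for categorical moderators such as sex or village, but the point is secondary.

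Finally, omitting factors balanced by design leaves the estimate essentially unbiased and errs on the conservative side. All of this stands and limits the size of the problem. It does not supply the missing threshold, fix the model across outcomes, or exempt the balancing factors.

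**Conclusion.** The point holds as a weakness in pre-specification. The protocol states a rule under which both balancing factors can be removed on the evidence of the data, by a criterion with no threshold that can be judged on the treatment estimate. It should be corrected, but it does not threaten the trial's validity.

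Under the rule as written, type I error stays near 5–7% even with deliberate picking and near 5% with mechanical use. When a balancing factor is dropped, the usual cost is a small loss of precision and a slightly conservative test. The 11-point power loss (94.1% versus 83.5%) belongs to always omitting strong factors, which is not the plan.

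These sizes rest on assumed prognostic strengths and on simulations with individual-level regression and no residual cluster effect. The textual conflict between the two sections does not depend on them.

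**What to change.** For the primary outcomes, and preferably the secondary ones, fix one model containing arm, baseline score, village, child age and the cluster random effect, with none of these subject to removal. The expressive picture test is given only to children aged 30–45 months, so the age band is constant there; use continuous age or omit the band for that outcome.

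Name any further covariates (sex, asset index, caregiver cognition) in or out beforehand, without significance testing. Keep treatment-by-moderator terms in the models of the Mediator and Moderator Analyses section. Data-driven selection can remain as a labelled sensitivity analysis.

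The statistical cost is 12 − 1 = 11 degrees of freedom for village per contrast, against about 295 dyads for most outcomes and fewer for the expressive test. The drafting cost is a sentence or two. Because data collection ended in September 2024 and analysis is in progress, the change should be dated and reported as made after data collection, with a statement of whether outcome data by arm had been seen.

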#### Mediator and Moderator Analyses

Mediator analysis will discern whether improvement in caregiver sensitivity mediates intervention effects on child outcomes. In addition, we will investigate whether improvements in parental sensitivity mediate advancements in reductions of parental stress. Mediation analyses will be conducted using the product-of-coefficients approach (a series of path models within the mixed-effects framework). CIs will be obtained using bootstrapping.

To assess moderation, interaction terms between the intervention and possible moderators will be included in the model. Subsequently, the significance of the interaction will be tested. In moderator analyses, we will also conduct a subgroup investigation to identify variations in the differential effectiveness of the intervention across subgroups. Subgroup analyses will be conducted with respect to the number of sessions attended, child sex, living standard, and the cognitive abilities of the caregiver.

#### Statistical Power

The required sample size was calculated according to accepted mathematical principles (48,49].

The sample size in each of the 3 arms of the study was computed using the following formula:

where α of .05 is the significance level, ...1–β (.80) is the power of the test, and *z*_1–α/4_ (2.24) and z_1–β_ (0.84) are quantiles of the standard normal distribution. The significance level α of .05 is divided by 4—the number of comparisons performed while primary hypotheses are tested (in fact, this is the so-called Bonferroni correction). All tests have 1-sided alternatives. On the basis of the previous meta-analytic studies [52,53], power is guaranteed for the effect size of 0.5. Finally, *DE* is the so-called design effect. It takes into account the clustered nature of data and is computed using the following formula:

DE = 1 + ([cv2 + 1]m –1)ICC

where the *m* value of 3 is the expected average cluster size, *ICC* is the intracluster correlation coefficient, and *cv* is the coefficient of variation of the cluster size. We set the *IC*C at 0.05—more than twice the commonly reported value of approximately 0.02 in comparable parenting studies. This higher value inflates the design effect and, in turn, the required sample size, providing a buffer that preserves statistical power. The value of *cv*^2^=2/9 was used, corresponding to a discrete uniform distribution of cluster sizes from 1 to 5. This range reflects both the settlement layout and our clustering procedure, which aimed to retain as many eligible households as possible while keeping clusters compact (refer to the Eligibility, Recruitment, and Randomization section). Substituting these values into the formula mentioned earlier, one obtains a *DE* of 1.13.

Taking into account a potential attrition rate of up to 15%, the required sample size of each arm is 100. Observations with missing values of the outcome variable will be excluded from the analysis that deals with the given outcome but could still be included in other analyses. Missing values in covariates will be substituted by their regression estimates based on other covariates. The impact of the substitution will be discussed by comparing the current estimates with those obtained if the observations with missing values were excluded.

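### The sample size is computed for 1-sided tests but the analysis plan fixes 2-sided tests, so 100 per arm does not give the stated 80% power

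*Protocol article*

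**What the plan says.** Two subsections under Data Analysis in the protocol article bear on this.

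- **Statistical Analysis Plan:** "Hypothesis tests will be 2-sided with α of .05". The next paragraph sets the multiplicity rule: "For the primary outcomes, we will use the Holm-Bonferroni method to adjust *P* values". No separate sidedness is given for the primary outcomes.
- **Statistical Power:** the per-arm size uses z(1−α/4) = 2.24 and z(1−β) = 0.84. The divisor is explained: "The significance level α of .05 is divided by 4—the number of comparisons performed while primary hypotheses are tested", and it is called a Bonferroni correction. Then: "All tests have 1-sided alternatives". With an effect size of 0.5, a design effect of 1.13 and up to 15% attrition, the section concludes that "the required sample size of each arm is 100", for a power of .80.

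**The concern.** A 1-sided test at .05/4 uses the quantile z(1−.05/4) = 2.24. A 2-sided test with the same four-fold correction uses z(1−.05/8) = 2.50. The sample size therefore rests on a less demanding criterion than the one the analysis section sets.

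Two things are at stake. First, the stated 80% power at 100 per arm would be wrong for the planned tests. Second, sidedness affects the result. In the expected direction, a 1-sided P value is half the 2-sided one for a symmetric statistic. At a first Holm step with 4 comparisons, a 2-sided P between .0125 and .025 fails under one sentence and passes under the other. Sidedness also decides whether a difference favouring a control arm can be declared, which matters in a trial with an active control. According to the Results section, data collection ended in September 2024 and analysis is under way, so either sentence could be cited once the data are known.

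**Working it through.** **Inputs** (Statistical Power section unless noted)

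- Overall α = .05, 4 comparisons, so .0125 per comparison
- Power .80, z = 0.8416
- Standardised effect size 0.5
- Average cluster size m = 3, ICC = 0.05, cv² = 2/9
- Attrition 15%
- 443 caregivers included (Eligibility, Recruitment, and Randomization section); arm sizes are not given, so an equal split of 443/3 = 147.7 is assumed

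The displayed sample-size formula did not survive in the text available for review. The standard form for comparing two means is assumed: n = 2(z_α + z_β)² / 0.5² × DE, then inflated for attrition. The attrition convention is not stated, so both common ones are shown.

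**Step 1. Design effect**

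DE = 1 + ((2/9 + 1) × 3 − 1) × 0.05 = 1.133, which agrees with the plan's 1.13.

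**Step 2. Required size per arm**

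| | 1-sided at .0125 (as in Statistical Power) | 2-sided at .0125 (as in Statistical Analysis Plan) |
|---|---|---|
| z_α | 2.241 | 2.498 |
| n before DE = 8 × (z_α + 0.8416)² | 76.0 | 89.2 |
| × 1.133 | 86.2 | 101.1 |
| ÷ 0.85 | 101.4 | 118.9, so 119 |
| × 1.15 | 99.1 | 116.3, so 117 |

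The 1-sided column reproduces the plan's 100 within rounding under either convention, which supports the assumed formula. The 2-sided column does not.

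**Step 3. Power at 100 per arm**

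Effective n = 100 × 0.85 / 1.133 = 75 per arm. The expected z statistic is 0.5 × √(75/2) = 3.062.

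- 1-sided: Φ(3.062 − 2.241) = 79.4%
- 2-sided: Φ(3.062 − 2.498) = 71.4%

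The effect detectable 2-sided with 80% power at this size is (2.498 + 0.8416) × √(2/75) = 0.545, not 0.5.

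**Step 4. Power for the number included**

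Effective n = 147.7 × 0.85 / 1.133 = 110.75 per arm. The expected z statistic is 0.5 × √(110.75/2) = 3.721. Two-sided power = Φ(3.721 − 2.498) = 88.9%.

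**Step 5. Can 2.24 be read as a 2-sided quantile?**

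Numerically, yes: z(1−.05/4) is the 2-sided quantile for 2 comparisons, and 100 per arm would then be right. The text excludes this reading, because it says that the 4 counts the comparisons and that the alternatives are 1-sided.

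**The case against.** The strongest reply is that the shortfall belongs to a trial of 100 per arm that was not run. With 443 included, 2-sided power is about 89% on the plan's assumptions. This stands, and it limits the finding to the stated justification and the unresolved sidedness. It does not reconcile the two sections.

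A second reply is that the analysis section looks forward and is the operative one, while the power section only explains a past calculation. That is the natural reading of which rule should prevail. But the power section does not present 1-sidedness as a planning device; it says that all tests have 1-sided alternatives.

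A third is that nothing was miscalculated. That is true of the sum: 100 follows from the power section's own inputs. The figure is wrong for the tests that the analysis section specifies.

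A fourth is that adjustment for baseline scores would recover power. At 100 per arm, an assumed baseline-outcome correlation of 0.40 divides the expected z statistic by √(1 − 0.16), giving 3.062/0.917 = 3.341 and Φ(3.341 − 2.498) = 80%. The same calculation gives 76% at 0.30 and 85% at 0.50. The document states no correlation and its calculation claims no such gain, so this cannot support the stated figure.

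Two cautions apply to the corrected numbers. The 89% is for a measure taken on all children. The direct expressive-language test is limited to children aged 30 to 45 months, and if half the sample qualifies (an assumption, keeping DE at 1.133) its 2-sided power is about 55%. The count of 4 comparisons is also taken from the plan as given; with 8, for instance if both postintervention assessments count, the 2-sided requirement would be about 136 per arm and power for the 443 about 84%.

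**Conclusion.** The concern holds. The two sections contradict each other on the sidedness of the primary tests, and the stated size and power match only the 1-sided version. Under 2-sided tests the requirement is 119 per arm (357 in total) if attrition is handled by dividing by 0.85, or 117 per arm (351 in total) if by multiplying by 1.15, against the stated 100 (300 in total). Power at 100 per arm is about 71%, roughly 9 points below the stated 80%.

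These figures rest on the standard two-means formula, on the plan's own effect size, ICC, attrition and 4 comparisons, and on no gain from baseline adjustment or later Holm steps. The finding does not show that the trial as run lacks power.

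**What to change.** - In Statistical Power, remove the sentence stating 1-sided alternatives as a description of the tests, and confirm that the primary tests are 2-sided, as in Statistical Analysis Plan.
- Replace z(1−α/4) = 2.24 with z(1−α/8) = 2.50 for the 4 comparisons, and restate the required size as 119 per arm (or 117), naming the attrition convention.
- If the record of how the trial was sized is to be kept, report 100 per arm explicitly as the 1-sided planning figure, beside the 2-sided one.
- Report 2-sided power for the 443 included, using the actual arm sizes, and say that it applies to measures taken on all children.
- Make the correction, with a date, before the primary results are unblinded to the analyst, or disclose that it came later.

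The cost is a few sentences. The design, the enrolment and the data collection do not change. The required size looks less favourable, but the number included already exceeds it.
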